## Abstract

**Introduction:**

Women with high-risk pregnancies (eg, pre-eclampsia, imminent preterm birth) are often hospitalised due to the need for foetal and maternal monitoring. They are monitored for 30–45 min up to three times a day with conventional cardiotocography (CTG). In the meantime, they reside at the hospital, but the foetal status is not monitored. Continuous foetal monitoring is currently not recommended using CTG, due to the potential temperature rise from consistent exposure to ultrasound waves. For safe 24/7 monitoring, newly developed devices using non-invasive electrophysiological cardiotocography (eCTG) instead of conventional CTG offer a promising alternative. Previous research into eCTG has shown favourable results in monitoring foetal heart rate throughout both pregnancy and labour. This study aims to investigate the effect of implementing continuous antepartum eCTG monitoring in hospitalised high-risk pregnancies on perinatal and maternal outcome.

**Methods and analysis:**

In this single centre prospective cohort intervention random sampling study, eligible women will be included on the Obstetric High Care of Máxima MC Veldhoven, the Netherlands. In total, 511 pregnant women with a singleton pregnancy between 23+0 and 32+0 weeks of gestation requiring hospitalisation will be recruited. Eligible women will be prospectively included in the cohort receiving standard treatment: intermittent CTG monitoring. From these women, a random sample of the prospective cohort will be offered a new monitoring method: 24/7 eCTG monitoring. For the eCTG monitoring, a wireless abdominal electrode patch, the Nemo Foetal Monitoring System will be used. Additional data from a historical cohort (2014–2019) of 1400 women receiving standard treatment will be included. Perinatal and maternal outcome, along with satisfaction levels of both patient and caregivers, will be compared between groups.

**Ethics and dissemination:**

The study is registered on 18 October 2022 to the Central Committee on Research Involving Human Subjects (NL82869.015.22) via https://www.toetsingonline.nl/to/ccmo_monitor.nsf/conceptabr?OpenForm and approved by the Medical Ethics Committee of Máxima MC (W22.070) on 7 November 2023. Results of the study will be disseminated in peer-reviewed scientific journals and conference presentations.

**Trial registration number:**

NCT06151613.

STRENGTHS AND LIMITATIONS OF THIS STUDYContinuous antepartum cardiotocographic (CTG) monitoring is implemented using a CE (Conformité Européenne)-certified device already in clinical use, and is compared to standard care (intermittent CTG monitoring).The cohort intervention random sampling study design allows inclusion of both prospective and retrospective data, reducing study exposure.Signal quality of electrophysiological CTG (eCTG) may be reduced between 28 and 32 weeks of gestation due to vernix caseosa, potentially requiring a switch to conventional CTG.Signal loss and switch rate between monitoring methods are systematically documented.Interpretation of preterm eCTG traces is based on literature-informed standard operating procedure and daily expert review.

## Introduction

 During pregnancy, maternal or foetal complications might arise, putting the mother and fetus in danger. When complications are diagnosed, pregnant women are often hospitalised for close monitoring of the maternal and foetal condition. One of the tools widely used to determine foetal well-being is cardiotocography (CTG). This is a combined external measurement method using two transducers that measure foetal heart rate (FHR) by the use of Doppler ultrasound (DU) and uterine activity by the use of tocodynamometry (TOCO). Despite its global utilisation, CTG has certain limitations. One of the drawbacks is the poor signal quality of DU and TOCO due to maternal and foetal movements. This arises particularly when monitoring preterm fetuses, multiple gestations and women with high body mass index (BMI).^1^,^4^ Additionally, despite the widespread use of CTG, there has been no reduction in the perinatal mortality rate. The above-mentioned limitations of CTG raise many questions as to how foetal monitoring can be optimised to improve perinatal outcomes. Due to a knowledge gap regarding preterm antepartum monitoring, clinical practice guidelines for CTG monitoring of preterm fetuses have not yet been developed. However, there are observational studies about antepartum CTG monitoring. These observational studies suggest that non-reassuring CTG traces are associated with adverse perinatal outcomes.^5^ The time interval between non-reassuring antepartum CTG traces and sudden foetal death can be only days to hours.^6^,^8^ This short time interval makes the current intermittent use of conventional CTG monitoring (one to three times a day for 30–45 min) inadequate for timely detection of foetal compromise. The use of continuous monitoring could potentially be a solution for optimising perinatal outcomes in preterm antepartum care. Not much is known about continuous antepartum monitoring. Nonetheless, a recent study claims twenty-four-hour CTG was found to be a good screening method to detect early onset hypoxia and thus recognise a fetus at distress early.^9^ Conventional CTG monitoring could not be used continuously in this study, due to the possibility of rise in foetal tissue temperature, resulting from constant exposure to ultrasound waves.^10 11^ Therefore, a new monitoring technique was used. Using this new technique based on electrophysiology, it was possible to safely assess FHR continuously.^12^ One of the devices that enables continuous non-invasive electrophysiological CTG (eCTG) monitoring is the NFMS (Nemo Foetal Monitoring System).^13 14^ In addition to the potential for continuous monitoring by eCTG, it has several additional advantages over conventional CTG monitoring. First, the intrapartum use of eCTG showed a reliable FHR in >95% of the time.^12^ When comparing this to DU used in conventional CTG monitoring, eCTG is far more reliable and accurate.^12^ Whether the eCTG also provides a reliable and accurate registration for preterm antepartum surveillance requires further examination. Second, eCTG monitoring is especially suited for the increasing number of women with obesity, where conventional CTG monitoring often fails.^23 15^,^18^ Additionally, there is no need to reposition the patch, whereas the transducers of conventional CTG often need to be repositioned due to the movements of the fetus. Disadvantages of eCTG are that preparation of the abdomen with abrasive paper can cause skin irritation and that eCTG cannot be used by women with a pacemaker, due to possible signal interference. Moreover, the performance of eCTG might be reduced in women between 28 and 32 weeks of gestation, due to lower quality of the non-invasive foetal electrocardiographic (NI-fECG) recordings resulting from the vernix caseosa impeding signal transmission.^19^ These (dis)advantages must be taken into account when introducing eCTG in clinical care. In order to improve perinatal outcomes through prevention of unnecessary or delayed interventions by implementing continuous monitoring, we set up the NIEM-O study (non-invasive electrophysiological monitoring on the Obstetric High Care). The aim of the study is to evaluate the effect of continuous antepartum eCTG monitoring on severe perinatal morbidity and mortality, by comparing with conventional intermittent CTG monitoring.

## Methods and analysis

The study is a single centre, prospective cohort intervention random sampling study (CIRSS) with historical controls: the NIEM-O study. Pregnant women will be recruited from the Máxima Medical Centre (MMC), a tertiary obstetric care hospital in Veldhoven, the Netherlands. Inclusion starts at the end of 2023, and is expected to take at least 2 years. Pregnant women will be recruited between 23 and 32 gestational age (GA) when they are admitted to the obstetric high care (OHC). The study protocol (version 9) is approved by the Medical Ethics Committee of Máxima MC (W22.070/NL82869.015.22).

### Study objectives

The primary objective of the study is to evaluate the effect of continuous antepartum eCTG monitoring on severe perinatal morbidity and mortality, by comparing with conventional intermittent CTG monitoring. The objectives are investigated in preterm fetuses (GA 23–32 weeks) whose mothers are admitted to the OHC. The primary study outcome is a composite outcome consisting of (1) Perinatal mortality, defined by the WHO as: deaths that occur after a gestational age of ≥22 weeks or, if unknown >500 gram, until 28 days after birth^20^ and (2) Major neonatal morbidity assessed at the time point when the neonate is discharged from the hospital.^21^ Major neonatal morbidity is defined as either: intraventricular haemorrhage (IVH) grade three or more,^22 23^ periventricular leukomalacia (PVL) grade two or more,^24 25^ moderate or severe bronchopulmonary dysplasia (BPD),^26^,^28^ necrotising enterocolitis (NEC) grade two or more,^29 30^ or retinopathy of prematurity (ROP) necessitating laser therapy.^31^ Secondary study objectives are the effect of continuous antepartum eCTG compared with conventional intermittent CTG monitoring on maternal mortality, neonatal morbidity, satisfaction for both patient and caregiver, duration of pregnancy, the need to switch between monitoring methods (either from eCTG to CTG or vice versa), timing and number of obstetric interventions, duration of admission at the OHC and admission and duration of admission at the neonatal intensive care unit. Demographics will be obtained from the electronic patient file. The secondary outcomes are defined as follows: maternal mortality as defined by the WHO^32^: any death from any cause related to or aggravated by pregnancy or its management (excluding accidental or incidental causes) during pregnancy and childbirth or within 42 days of termination of pregnancy, irrespective of the duration and the site of the pregnancy. Neonatal morbidity, excluding major neonatal morbidity described as primary outcome, is defined as: Any health condition attributed to and/or aggravated by birth, assessed at the time point when the neonate is discharged from the hospital^21^ or—if discharged within 4 weeks after birth—at 4 weeks after birth, that has negative outcomes to the neonatal well-being (ie, IVH grade 1–2, PVL grade 1, mild BPD, NEC grade 1, ROP (any grade)) not necessitating laser therapy, hypoxic ischaemic encephalopathy, neonatal seizures, neonatal sepsis (culture proven), need for intubation on the delivery room, mechanical ventilation within the first 72 hours after birth, antibiotics within the first 72 hours after birth, spontaneous intestinal perforation necessitating surgery, surfactant treatment, Apgar score <7 after 5 min, severe metabolic acidosis (pH <7.05 and base deficit ≥12 mmol/L). This definition of severe metabolic acidosis is set at pH <7.10 and base excess ≥12 mmol/L in cases with only an umbilical vein sample (one available blood gas sample or the pH difference between two samples below 0.03^33^). Next to the study objectives described above, the data that is gathered in this study will be used to develop and verify mathematical models that aim at the prediction of time to (premature) birth and at automated detection of foetal movements.

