#### Retrospective recruitment

In order to strengthen the comparison of the two groups (continuous eCTG monitoring and conventional intermittent CTG monitoring), additional data from women who received standard treatment (conventional intermittent CTG monitoring) in Máxima MC Veldhoven, the Netherlands in 2014–2019 will be collected retrospectively. Data will be derived from electronic patient records (EPRs).

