### Sample size

A total of 1911 patients (comprised of 511 prospectively included women and 1400 historical controls) would be sufficient to evaluate the primary objective. Incidence of the composite outcome is based on numbers of perinatal morbidity and mortality of MMC from 2019, combined with a literature-based estimation of the simultaneous occurrence of the perinatal comorbidities and mortality.^40^,^43^ Due to the unknown effect of COVID on perinatal and maternal outcomes,^44^ numbers from MMC of 2020–2021 are not included in the sample size calculation. This resulted in a rounded estimated composite outcome of 17%. Based on clinical experience, an effect size of 6% is expected. To detect this effect size with a power of 80% and a type I error of 5%, a group of 511 women will be invited for the prospective cohort. Of these 511 women, 464 women (90.8%) will be in the sampled study arm and 47 women (9.2%) in the non-sampled study arm. Based on clinical experience, an estimation of 80% acceptance rate for data collection in the sampled and non-sampled group was made (resulting in 372 women and 37 women respectively). Among the 372 women who agreed to data collection in the sampled group, it is expected that 90% will accept and receive eCTG monitoring (335 women) and 10% (37 women) will decline eCTG monitoring and therefore receive CTG monitoring. All 37 women in the non-sampled group will receive standard monitoring. For the retrospective cohort, a total of 1400 participants will be included (figure 3). No dropout rate is calculated, due to continuation of the study and sampling until the requested sample size (of both groups) is reached.

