### Study limitations

It is unknown if reference standards for CTG patterns of term fetuses as stated in current literature can be applied to fetuses during the preterm period.^46^ Also, little to no research is available on the use and interpretation of eCFM for a prolonged period of time.^47^ Before study initiation, all clinical staff involved in CTG interpretation will undergo standardised training sessions based on current literature and internal guidelines.^4649^,^53^ Additionally, daily multidisciplinary meetings will be held to discuss CTG traces, fostering consensus and calibration among attending gynaecologists. These procedures will be documented in an SOP. Accurate determination of the foetal condition based on the CTG trace may be subject to inter-observer variability, possibly influencing perinatal outcome.^46^ However, this concerns both the use of conventional intermittent CTG as well as the continuous eCTG monitoring method. The vernix caseosa, a fatty layer covering the fetus between 28 and 32 weeks GA, may dim the foetal cardiac signal and might lead to insufficient data for NI-fECG analysis.^39^ This possible decrease in signal quality might result in a necessity to switch to conventional CTG monitoring. No risks are involved in switching to the conventional system. Signal loss and switch rate will be documented and are part of the secondary objectives of the study. The CIRSS study design deviates from a standard randomised clinical trial, where both treatment arms are randomised to patients. The inclusion rate of patients is expected to be substantially larger than for a randomised controlled trial, since (almost) all women who participate and receive standard care are automatically included. By making use of causal inference approaches for observational studies, we are able to include patients with standard care from the past, reducing the sample size and the number of patients exposed to the study setting. Also, since women receiving standard care are uninformed of new interventions, we believe the current approach more accurately represents normal practice, while putting as little burden on the women and caregiver as possible. To account for potential differences between the historical and prospective cohorts, including changes in clinical practice over time (eg, due to COVID-19), we applied a propensity score adjustment strategy and conducted sensitivity analyses to ensure methodological robustness and reduce bias.

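### The ROP component of the primary composite is tied to laser treatment, so a shift in treatment method between eras would bias a comparison in which era nearly coincides with arm

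*Protocol article*

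**What the plan says.** Under Study objectives, the primary outcome combines perinatal mortality with "Major neonatal morbidity assessed at the time point when the neonate is discharged from the hospital". IVH, PVL and NEC enter by a minimum grade and BPD by severity category. ROP enters as "retinopathy of prematurity (ROP) necessitating laser therapy". The secondary neonatal morbidity outcome takes the complement: "ROP (any grade)) not necessitating laser therapy".

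On timing, Methods and analysis states: "Inclusion starts at the end of 2023, and is expected to take at least 2 years". Retrospective recruitment states that data on standard-care women "in Máxima MC Veldhoven, the Netherlands in 2014–2019 will be collected retrospectively". Sample size gives "A total of 1911 patients (comprised of 511 prospectively included women and 1400 historical controls", with 335 women expected to receive eCTG and 37 + 37 prospective women expected to receive CTG.

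Study limitations mentions possible differences between the cohorts, "including changes in clinical practice over time (eg, due to COVID-19", and answers them with propensity score adjustment and sensitivity analyses. Statistical analysis lists maternal, foetal and care-related covariates for the score and plans to analyse the components of the composite separately.

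**The concern.** A treatment-based component mixes how severe the disease was with how it was managed. Taken literally, an infant with severe ROP treated by something other than laser is not a primary event. Because the secondary category covers any grade, that infant is counted there as lesser morbidity.

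In a concurrent randomised comparison, a change in treatment method would affect both arms alike. Here nearly all the comparator comes from an earlier era than the intervention group, so a change between eras would look like a treatment effect.

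The planned adjustment does not reach this problem. A propensity score balances who is in each group; it does not make an outcome definition capture the same cases in two periods. None of the covariates given as examples describes neonatal ROP treatment. Analysing ROP as its own endpoint under the same wording would reproduce the shift, where it could be read as benefit.

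**Working it through.** **Inputs from the article.** Control event rate 17%; effect 6%, read as absolute (17% to 11%); power 80%; type I error 5%, taken as two-sided because the article does not say. eCTG women: 335. CTG women: 1400 + 37 + 37 = 1474.

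**Step 1: reproduce the plan's power.** Two-proportion test, pooled variance under the null:
- Pooled rate = (335 × 0.11 + 1474 × 0.17) / 1809 = 0.1589.
- SE under the null = √[0.1589 × 0.8411 × (1/335 + 1/1474)] = 0.02213.
- SE under the alternative = √[0.11 × 0.89/335 + 0.17 × 0.83/1474] = 0.01970.
- Power = Φ[(0.06 − 1.96 × 0.02213) / 0.01970] = Φ(0.844) = 80.1%.

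The stated 80% is reproduced, which supports 335 versus 1474 as the planned comparison.

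**Step 2: overlap of era and arm.** All 335 eCTG women are prospective. Of the CTG women, 1400/1474 = 95.0% are historical and 74/1474 = 5.0% are concurrent.

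**Step 3: bias if treatment moves away from laser.** Let *m* be the proportion of infants for whom ROP is the only component and who would be treated by laser in the earlier era but by another method in the later one. Only such infants matter: one who dies, or has another component, still counts. With no true effect:
- eCTG rate = 17% − *m*
- CTG rate = 17% − *m* × 74/1474
- Spurious difference = *m* × 1400/1474 = 0.95 *m*, favouring eCTG

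**Step 4: size.** The article gives no ROP rate and no treatment mix, so *m* is assumed over 0.25 to 2 percentage points. Type I error is the two-sided rejection probability of the Step 1 test at these rates.

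| Assumed *m* (points) | eCTG events lost (335 × *m*) | Spurious difference (points) | Share of planned 6 points | Type I error |
|---|---|---|---|---|
| 0.25 | 0.8 | 0.24 | 4% | 5.0% |
| 0.5 | 1.7 | 0.47 | 8% | 5.3% |
| 1 | 3.4 | 0.95 | 16% | 6.7% |
| 2 | 6.7 | 1.90 | 32% | 12.7% |

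Worked row, *m* = 1 point: rates 16.00% and 16.95%, difference 0.95 points, SE under the null 0.02261, SE of the difference 0.02229. Rejection in favour of eCTG: 1 − Φ[(1.96 × 0.02261 − 0.0095)/0.02229] = 5.9%. Rejection against eCTG: 0.8%. Total 6.7%.

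**The case against.** **No change in ROP treatment is documented.** The article does not say that another method was used in either period. Its remark on practice over time is general and does not mention ROP, so a reader who infers that the authors expect a change in ROP treatment goes beyond the text. This objection stands: the point can only be conditional.

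***Necessitating* may mean reaching the threshold at which laser is indicated.** That is close to a severity criterion, and equally severe ROP treated otherwise would then still count. The source cited for the component, or the full protocol, may settle this; neither is at hand. The reading is fair and would soften the problem. It would still describe the threshold through one treatment, and whoever extracts the 2014–2019 records needs to know which reading applies.

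**Stronger readings are tempting.** A reader might infer that events would be lost from one arm only, that any change in method removes events, or that the bias necessarily favours eCTG. None of these holds. The 74 concurrent CTG women would be affected in the same way, a shift towards laser would add events and count against eCTG, and the direction of any change is unknown.

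**Partial safeguards exist.** The component-wise analysis would show a fall in laser-treated ROP, and ROP not requiring laser is recorded as a secondary outcome. This helps detection but leaves the primary definition unchanged. As defined, the secondary category also does not separate severe ROP treated by another method from mild ROP.

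**Conclusion.** The point holds as a conditional vulnerability in an otherwise reproducible design. The ROP component depends on treatment method, and 95% of the comparator belongs to an earlier era than the whole eCTG group. About 95% of any era-related shift in laser use would therefore become bias, and the planned analyses would not remove it.

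Its size rests entirely on the assumed *m*. Up to half a point of infants moved, the type I error stays at or near nominal (5.0% to 5.3%). It becomes noticeable at about 1 point (6.7%) and reaches 12.7% at 2 points. The calculation also assumes the literal reading of the definition, a shift away from laser, and an unadjusted two-proportion test.

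The documents do not support saying that the primary result will be biased, or that a particular share of the planned 6 points is artefact. This is an inexpensive improvement to an endpoint definition, not a demonstrated error.

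**What to change.** Define the primary ROP component independently of treatment method, either as ROP necessitating any treatment or as ROP at or above a fixed severity grade. Apply the same rule to historical and prospective records. Change the secondary category to its exact complement, and report the laser-only definition as a sensitivity analysis. State whether the criterion is treatment received or an indication met.

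The cost is an amendment to one component of the primary outcome in a study whose inclusion was due to start at the end of 2023, one additional field in record extraction for both cohorts, and a recheck of the event rate, since the article says of its inputs: "This resulted in a rounded estimated composite outcome of 17" per cent. The change concerns only how the endpoint is counted, not how ROP is treated.

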#### Prospective recruitment

Potential participants will be informed about the study by their obstetric healthcare professional when admitted to the hospital. First, the healthcare professionals will verify the inclusion and exclusion criteria (table 1), after which the women are added to the study using an encryption key. These women are part of the cohort study and receive standard care consisting of conventional intermittent CTG monitoring. A part of these women will be randomly sampled. This random sampling is conducted by the research team using a secure algorithm embedded in Research Manager (ISO 27001 certified). They will be offered the new treatment: continuous eCTG monitoring using the NFMS (figure 2). The women will either be part of the cohort study, thus receiving standard care consisting of conventional intermittent CTG monitoring, or they will be sampled for continuous eCTG monitoring using the NFMS. Appropriate explanation and written study information will be provided hereafter by the healthcare professional, and they will ask the researchers for further counselling. Non-sampled women will only receive information regarding the collection of their data in the cohort study. Sampled women will be informed about receiving continuous eCTG monitoring. A researcher will complete the informed consent (IC) procedure, including collecting written consent (for an example of the participant consent form, see online supplemental file 1). When the women do not wish to participate in the study, they will be excluded, their encrypted information will be obliterated and the exclusion will be anonymously documented. Once women are included, they are given the appropriate monitoring method. Five NFMS devices are available at the OHC of Máxima MC. When no NFMS device is available within 24 hours after sampling and inclusion, the sampled women will receive standard treatment within the study. For continuous monitoring, trained nursing staff will oversee device placement and signal quality checks during routine care. CTG traces are continuously displayed on a central monitoring system, where deviations from normal patterns trigger automated alarms to alert clinical staff. In addition, CTG traces are systematically assessed by physicians at least four times per 24 hours at predefined intervals, partly retrospectively, and more frequently if clinically indicated. These assessments follow a standard operating procedure (SOP) to ensure consistency and clinical relevance. If the eCTG recording does not provide sufficient signal quality for reliable monitoring, we will report this and, if needed, can be switched to standard CTG monitoring. This decision will be made on the clinical judgement of the attending gynaecologist. No literature was available on an acceptable signal loss threshold. The International Federation of Gynaecology and Obstetrics Guidelines advises switching monitoring methods in intrapartum monitoring when a signal loss threshold of 20% is reached.^35^ Based on this, a standardised protocol for switching to conventional CTG will be implemented when signal loss exceeds 20%, or when clinical judgement deems the eCTG trace insufficient for reliable interpretation. This protocol will be documented and monitored throughout the study. Women who decline to be part of the cohort will receive standard care: conventional CTG monitoring without data collection for research. All prospectively included women will receive a digital invitation to two digital surveys. Women are asked to fill in the first survey about their experience with the received monitoring method—EQ5D5L questionnaire^36^—on the first day after admission, and the second survey about their experience—D-QUEST^37^—on the last day of admission. Although the patient satisfaction surveys are administered at admission and discharge, all participants are followed up until (at least) 4 weeks postpartum. During this period, patients have the opportunity to share additional reflections or concerns with their care team, which may provide further qualitative insights into their experience with the monitoring method.

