### Statistical analysis

For the primary and secondary outcomes, based on the demographics, characteristics of the women and their baseline outcomes, a propensity score will be created. This will be used to correct for possible selection bias that may occur due to (1) the group of women who are offered eCTG but receive CTG (either by choice or circumstances) or (2) the retrospective and prospective nature of the study. Thus, a per-protocol analysis with propensity score adjustment will be considered. The propensity score models will include maternal characteristics (eg, age, BMI, parity, ethnicity), foetal indicators (eg, gestational age, foetal growth restriction, Doppler abnormalities) and care-related variables (eg, indication for admission, medication use, duration of hospitalisation). These covariates were selected based on clinical relevance and availability across both cohorts. For categorical outcomes, a logistic regression analysis will be applied to estimate the treatment effect corrected for the propensity score. For numerical outcome values, a general linear model will be applied with an appropriate probability distribution link function and the sandwich estimator to estimate a treatment effect corrected for the propensity score. For time-to-event outcome, a Cox proportional hazards model will be used with a sandwich estimator to estimate a treatment effect corrected for the propensity score. For the data gathered from the questionnaires, standard statistical tests will be used (χ^2^, t-test, Mann-Whitney tests) to determine a difference between the two treatment groups. A propensity score approach will be applied as well if large imbalances between characteristics are present between CTG and eCTG participants. Several sensitivity analyses are being anticipated. The combined endpoint will be analysed as separate end-points. Several subgroup analyses are investigated (eg, obesity). A p value of <0.05 is considered statistically significant unless otherwise specified. When possible, 95% CIs will be calculated for the reported measures of effect. Missing data will be evaluated and reported. Limited missing data is expected, and if missingness is less than 5%, list-wise deletion will be used. Otherwise, multiple imputation (eg, predictive mean matching) will be used. The imputation will be repeated at least 10 times and Rubin’s rule will be used to combine estimates and standard errors from the imputed data.

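### Need to switch is set as an eCTG-versus-CTG outcome, but 97.5% of the planned CTG comparator has no stated route to eCTG, so the contrast would mainly reflect access to the device

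*Protocol article*

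**What the plan says.** **Status of the outcome.** Study objectives introduces the secondary objectives as effects of continuous eCTG compared with intermittent CTG, and includes "the need to switch between monitoring methods (either from eCTG to CTG or vice versa" in that list. Study limitations repeats that switch rate is part of the secondary objectives and will be documented.

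**Planned analysis.** Statistical analysis opens with "For the primary and secondary outcomes, based on the demographics, characteristics of the women and their baseline outcomes, a propensity score will be created". It then gives a general rule by outcome type: "For categorical outcomes, a logistic regression analysis will be applied to estimate the treatment effect corrected for the propensity score". Only questionnaire data are handled separately. No model is named for switching.

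**Routes described.** Under Prospective recruitment, "a standardised protocol for switching to conventional CTG will be implemented when signal loss exceeds 20" per cent, or when clinical judgement finds the eCTG trace inadequate. Ethics and risk assessment allows a move to conventional CTG for skin irritation. Study limitations foresees the same move when vernix weakens the signal. Women readmitted to the ward stay in their monitoring group.

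**The CTG comparator.** It has these parts:
- historical controls from 2014–2019, described as "women who received standard treatment (conventional intermittent CTG monitoring");
- non-sampled women: "Non-sampled women will only receive information regarding the collection of their data in the cohort study";
- sampled women who decline: "10% (37 women) will decline eCTG monitoring and therefore receive CTG monitoring";
- sampled women for whom no device is free: "When no NFMS device is available within 24 hours after sampling and inclusion, the sampled women will receive standard treatment within the study". No number is given for these.

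**The concern.** A between-group comparison of switching is informative only if women in both groups could switch. Here the alternative to eCTG is conventional CTG, which is always at hand. The alternative to conventional CTG is eCTG, and nearly all the CTG women have no stated way to reach it. A poor CTG trace in a historical or non-sampled woman cannot show up as a switch, however badly CTG performed. A poor eCTG trace can.

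The propensity score balances measured characteristics of the women. It does not give a 2014–2019 control a device to switch to. If the general rule were followed, the reported effect could make eCTG look much more prone to abandonment than CTG for a reason unrelated to how well either method works. The figure that clinicians need, how often eCTG has to be given up, requires no comparator.

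**Working it through.** **1. Check that the comparator is the planned one.** From Sample size: 335 women receive eCTG; CTG women are 1,400 historical + 37 non-sampled + 37 decliners = 1,474. The plan states 80% power at 5% type I error for a 17% composite rate and an effect of 6%. Reading these as 17% versus 11%, two-sided, with the normal approximation and pooled null variance, 1,474 versus 335 gives power 0.801. That reproduces the stated 80%, so 1,474 is the comparator the plan intends.

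**2. Share with no stated route to eCTG.** (1,400 + 37) / 1,474 = 1,437 / 1,474 = 97.5%. Historical controls alone are 1,400 / 1,474 = 95.0%. If *m* further sampled women stay on CTG because no device is free, the share is 1,437 / (1,474 + *m*). The article gives no *m*, so a range is assumed:

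| Assumed *m* | Share with no stated route |
|---|---|
| 0 | 97.5% |
| 17 | 96.4% |
| 34 | 95.3% |
| 67 | 93.3% |

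**3. What a crude odds ratio would do.** All switch counts are assumed, since the article gives none, and a logistic model is inferred from the general rule. With *k* of 335 switching on eCTG and *d* of 1,474 on CTG:

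OR = *k* (1,474 − *d*) / [(335 − *k*) *d*]

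| *k* | *d* = 1 | *d* = 2 | *d* = 4 |
|---|---|---|---|
| 17 | 79 | 39 | 20 |
| 34 | 166 | 83 | 42 |
| 67 | 368 | 184 | 92 |

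For *k* = 34 the Wald 95% CIs are 23–1,220, 20–348 and 15–118. With *k* = 34 and *d* = 0 there is no finite estimate; the exact conditional 95% interval runs from 42 with no upper limit. At the other end, *k* = 1 and *d* = 4 gives 1 × 1,470 / (334 × 4) = 1.1.

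**4. Separating access from performance.** Suppose, purely as an illustration, that 4 of the 37 decliners changed to eCTG (10.8%) while 34 of 335 eCTG women changed to CTG (10.1%).
- Against the 37 decliners: OR = 34 × 33 / (301 × 4) = 0.93.
- Against all 1,474: OR = 34 × 1,470 / (301 × 4) = 41.5.

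The switch counts are the same in both lines. The difference comes wholly from adding 1,437 women with no stated route.

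**5. The same outcome in one group.** Exact (Clopper–Pearson) 95% CIs for assumed counts among 335 eCTG starters:

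| Switches | Proportion | 95% CI |
|---|---|---|
| 17 | 5.1% | 3.0–8.0 |
| 34 | 10.1% | 7.1–13.9 |
| 67 | 20.0% | 15.8–24.7 |

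The planned eCTG group is large enough for a usable estimate.

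**The case against.** **The comparison may never be meant.** Wherever the article describes the handling of switching, it speaks of documenting and monitoring it. The comparative reading comes from a shared lead-in to a list and a general sentence in the analysis section, and the model for each secondary outcome is commonly left to an SAP. It is right that no model is named and that logistic regression is an inference. But the objectives do frame the item as an effect of eCTG versus CTG, and the general rule covers secondary outcomes with questionnaires as the only separate case.

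**The reverse direction is named.** The full protocol or the switching SOP may describe a move from CTG to eCTG, or the phrase may mean a return to eCTG after a temporary switch. Either is possible. A prospective procedure could matter for decliners and women without a free device, but it could not reach the 1,400 historical controls. A return to eCTG occurs only among women who started on it, which supports a one-group outcome.

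**Need could be measured in both groups.** Need to switch is not the same as having switched, and a criterion such as signal loss could be applied to both methods. That would be a sound alternative, but the article does not say need will be assessed this way in CTG women.

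**Stronger readings.** A reader might infer that the odds ratio will be very large whatever the device's performance. The documents do not support that: one eCTG switch against four CTG switches gives 1.1, and the ratio rises steeply with the number of eCTG switches. A reader might also infer that a move from CTG to eCTG is impossible for every CTG woman. The article states no such procedure, but decliners and women awaiting a device could plausibly change.

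**Conclusion.** The point holds as a minor one. As written, the plan puts switching among the between-group effects, while every switching procedure described runs one way and 97.5% of the planned CTG comparator has no stated route the other way (93.3% if as many as 67 further women stay on CTG for want of a device, an assumed figure). Such a contrast would mainly reflect access to the device, and propensity adjustment cannot repair it. Only the 97.5% follows from the documents. The size of any odds ratio, including whether it is finite, depends on switch counts that are not given, and the use of a logistic model is inferred. One secondary outcome is affected; the primary analysis and the sample size are not.

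**What to change.** - In Study objectives, take switching out of the list of eCTG-versus-CTG effects. Delete the words on the reverse direction, or define them as a return to eCTG after a switch to CTG.
- In Statistical analysis, add one sentence: among women who started eCTG, report the proportion with at least one switch to CTG with an exact 95% CI, overall and by gestational age at eCTG start (<28 and 28–32 weeks), with no test against CTG. Age must be fixed at eCTG start because it advances during admission.
- Ideally also report switches per day on eCTG, because a simple proportion ignores differing time on the device.

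**Cost.** Two wording changes. Switch rate is already to be documented, so the main proportion needs no extra patients or data; the daily rate also needs each woman's time on eCTG. The downside is that the study makes no comparative statement on switching.
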